## Abstract

**Background:**

The inappropriate use of multiple medications known as polypharmacy is a growing concern for older populations with comorbid conditions in India. Polypharmacy can lead to serious adverse health outcomes, increased health care costs, and reduced quality of life. Screening tools such as the Medication Appropriateness Index (MAI) and Screening Tool for Older Persons’ Prescriptions (STOPP) or Screening Tool to Alert to Right Treatment (START) criteria can help identify potentially inappropriate medications, and interventions such as medication review clinics and prescribing audits can help improve the appropriateness. A collaborative medication review (CMR) involving a team approach is important to ensure that patients receive the best possible care.

**Objective:**

The primary objective is to assess the feasibility of implementation of interdepartmental CMR to reduce potentially inappropriate medications in hospitalized older adults. The secondary objectives are to (1) explore the facilitators and barriers in this implementation from the health care providers’ perspective, (2) determine the costs involved in the implementation from a health system perspective, and (3) analyze the efficacy of interdepartmental CMR by using MAI, postdischarge adverse events, and number of medication-related admissions.

**Methods:**

This study consists of 5 phases aimed at improving CMR practices in India. Phase 1 focused on conducting a scoping review of CMR practices. Phase 2 involved creating standard operating procedures to establish a CMR team, delineating roles and responsibilities, and providing training. Phase 3 will evaluate the efficacy of CMR by using standardized tools such as MAI and STOPP/START criteria. Phase 4 assesses the challenges faced in implementing CMR. Finally, phase 5 analyzes the costs related to CMR implementation. This study employs a multicentered mixed methods approach, combining qualitative methods (in-depth interviews and focus group discussions) to explore implementation challenges and quantitative analysis through a quasi-experimental study involving 280 hospitalized older adults. It aims to measure costs and the reduction of potentially inappropriate medications post discharge.

**Results:**

This study received a grant from the Indian Council of Medical Research–Safe and Rational Use of Medicine Task Force in December 2023. All study preparatory approvals were obtained. Phase 1 and phase 2 were completed by December 2024. Phase 3 is scheduled to finish by June 2025. Phases 4 and 5 are planned for completion by August 2025. Final data analysis and manuscript submission are expected by December 2025.

**Conclusions:**

This study can provide insights into the implementation and effectiveness of CMR and help to understand the facilitators and barriers to implementing interdepartmental CMR and the cost incurred in its implementation. Interprofessional teams will collaboratively review and optimize medications for older patients with multimorbidity in India—a strategy expected to enhance care coordination, improve clinical outcomes, and reduce health care costs.

**Trial Registration:**

Clinical Trials Registry – India CTRI/2024/06/069220; https://ctri.nic.in/Clinicaltrials/pmaindet2.php?EncHid=OTgyNDg=&Enc=&userName=

## Introduction

Inappropriate polypharmacy refers to the use of multiple medications in a way that is not consistent with established treatment guidelines or that can increase the risk of adverse drug reactions, drug interactions, or other health problems. High-risk populations such as older adults and individuals with multiple chronic conditions are particularly vulnerable to inappropriate polypharmacy. In India, inappropriate polypharmacy in older adults is a growing concern due to the lack of awareness and regulations surrounding medication use. The prevalence of potentially inappropriate medicine use among the older Indian adult population is 28% [1]. The older adult population in India represents 8.6% (104 million) of the total population [2]. These patients often have multiple comorbidities, leading to the prescription of multiple medications. The consequences of inappropriate polypharmacy in high-risk populations can be serious and can include increased risk of falls, hospitalizations, and other adverse health outcomes. In addition, inappropriate polypharmacy can lead to increased health care costs and reduced quality of life for patients [3].

Many screening tools are available as either implicit (judgment-based) or explicit (criterion-based) tools to identify inappropriate polypharmacy [4]. Implicit tools such as the Medication Appropriateness Index (MAI) and Assessment of Underutilization of Medicine assess the prescribing quality of a physician’s prescription for an older adult. Explicit tools such as Beer’s criteria and the Screening Tool for Older Persons’ Prescriptions (STOPP) or the Screening Tool to Alert to Right Treatment (START) criteria have been developed from literature reviews, expert opinions, and consensus exercises, typically comprising a list of drugs to be avoided or added for older adult populations [5]. However, along with identifying the inappropriateness, choosing the best intervention to improve appropriate polypharmacy is a priority goal.

Improvements in inappropriate polypharmacy can be achieved by a wide range of interventions to address the complexity of the clinical situations and the individuality of the prescribers. In India, interventions to improve appropriate polypharmacy are needed to address specific problems related to multimorbidity, which need to be integrated into existing health care systems and embedded with interprofessional collaboration. Some of the interventions include educational programs for prescribers or consumers, medication review clinics and specific prescribing audits, and prescribing incentive schemes and regulatory interventions [6].

Effective polypharmacy interventions involving drug reviews require the consideration of several factors, including the hospital setting, health care professional, purpose and scope of review, criteria to guide review, tool to base drug review, and, finally, the method (manual of the clinical decision support system) used for drug review. The current literature distinguishes 3 types of drug reviews, namely, prescription reviews (performed without the patient), concordance and complication reviews, and clinical medication reviews (performed in the presence of the patients). However, in India, it is feasible to conduct only a prescription review on the basis of its convenience and feasibility [7].

Furthermore, drug reviews are usually formalized and driven either by implicit or explicit criteria. Owing to their usefulness, explicit or criteria-based screening tools are used most often to help the systematic assessment of medication appropriateness. Varas-Doval et al [8] conducted the ConSIGUE program, which assessed the impact and implementation of a medication review with follow-up for older patients with multiple medications. They suggested that the provision of a medication review with follow-up in collaboration with general medical practitioners and patients contributes to the improvement of older patients’ health status and reduces their problems related to the use of medicines [8]. Medication reviews have been shown to be a cost-effective strategy through a cost-utility analysis [9]. However, policy makers look for other economic evidence other than the cost-utility analysis in the process of considering a change in the health policy and a payment for the service.

Malet-Larrea et al [10] conducted a cluster randomized trial of a medication review with follow-up to ascertain its economic impact from a national health system perspective over 6 months. The cost-benefit ratio revealed that for every €1 (US $1.17) invested in a medication review with follow-up, a benefit of €3.3 (US $3.87) to €6.2 (US $7.28) was obtained. In fact, other studies [10] presented even greater cost-benefit ratios such as those included in a series of systematic reviews (1:34.61, 1:17.0, 1:25.95, and 1:75.84).

In India, physicians follow the theme of professional isolation in the management of patients with multimorbidity. This practice emanates from the interplay among 4 aspects of patient management, namely, disorganization and fragmentation of health care, inadequacy of guidelines and evidence-based medicine for multimorbidity, challenges in delivering patient-centered rather than disease-focused care, and barriers to shared decision-making.

Interdepartmental collaborative reviews may overcome all these barriers, allowing for a more comprehensive review of the patient’s medication needs, considering factors such as the patient’s medical history, current symptoms, and medication side effects. This study will evaluate the challenges in the implementation of an interdepartmental collaborative medication review (CMR) and the cost analysis of a planned CMR to prevent potentially inappropriate medications in the hospitalized older adult population.

## Methods

### Study Settings

This study is planned to be conducted over a period of 2 years in 5 phases chronologically (Figure 1). The study will be conducted at the Pondicherry Institute of Medical Sciences and Jawaharlal Institute of Postgraduate Medical Education and Research, Puducherry, India, in collaboration with Indian Council of Medical Research (ICMR)-National Institute of Epidemiology, Chennai, India, and ICMR headquarters, New Delhi. The scoping review (phase 1) on CMR is completed.

**Figure 1 figure1:**
[figure not shown]
Description of the 5 phases of the study. * denotes phases 3 and 4 will be conducted simultaneously. CMR: collaborative medication review; MAI: Medication Appropriateness Index; SOP: standard operating procedure; START: Screening Tool to Alert to Right Treatment; STOPP: Screening Tool for Older Persons’ Prescriptions.

### Phase 1: Scoping Review on CMR

We conducted a comprehensive search on databases, including PubMed, Cochrane Library, Clinicaltrials.gov, Global Index Medicus, Lens.org, and World Health Organization (WHO)-International Clinical Trials Registry Platform registries by using the following search terms: medication review, collaborative review, prescriptions, prescription drugs, and aged people. We included only English language studies. Two review authors independently extracted data from each included study via a predesigned data extraction form. We will attempt to contact the trial authors to request incompletely reported data. The following information was extracted: general information (study ID, date of extraction, title, authors, and source of study if not published), study characteristics (study settings, study design, participants, and inclusion/exclusion criteria used in the study), details of interventions, outcomes as described in the types of outcome measures above, and details necessary for the risk of bias assessment. Disagreements between review authors were resolved by discussion or by consultation with a third review author.

### Phase 2: Drafting Standard Operating Procedures to Formulate CMR Teams in the Indian Context

On the basis of the results of the scoping review, the standard operating procedures will be developed by the team of investigators. The scope of the standard operating procedures includes the composition (members) of the CMR team; training of the CMR team; frequency of the CMR team review meetings; details regarding the intervention, which includes the assessment of drug charts and conveyance of information regarding any medication inappropriateness to the treating clinicians as well as follow-up of the participants; and the documentation process. All the developed standard operating procedures were reviewed and approved by the principal investigator and the head of the institution.

### Phase 3: Assess the Efficacy of CMR

The efficacy of CMR is assessed via standardized tools such as MAI, START/STOPP criteria, and AT-HARM10 (Assessment Tool for identifying Hospital Admissions Related to Medications-10 items).

### Phase 4: Assessing the Challenges and Barriers

Phase 4 involves assessing the challenges and barriers in implementing CMR in the Indian health care setting.

### Study Design

#### Mixed Methods Study Design

##### Qualitative Component

In-depth interviews and focus group discussions (FGDs) were conducted to explore the facilitators and barriers to the implementation of interdepartmental CMR to reduce potentially inappropriate medications in hospitalized older patients.

##### Quantitative Component

The study design was quasi-experimental preinterventional and postinterventional with the following components: (1) costs incurred for the implementation of CMR in Indian health care settings and (2) MAI, reduction in the percentage of inappropriate medications, postdischarge adverse events, and medication-related admissions.

#### Study Period and Duration

Each participant’s participation will last from admission until 30 days after discharge from the hospital.

#### Study Participants

Health care providers at the 2 sites will be involved in the study to assess the facilitators and barriers in the implementation of interdepartmental CMR from their perspective. The prescriptions of both male and female older patients (aged 60 years and older) admitted to any medical or surgical ward at both study sites will be assessed to determine whether the participants meet the eligibility criteria after the medical records are reviewed.

### Study Eligibility Criteria

#### Inclusion Criteria

The inclusion criteria were as follows:

Male and female patients aged 60 years and older with multiple morbidities admitted to all medical and/or surgical specialty/subspecialty wards at the study sites.Patients visiting the study sites from places (villages/towns) within a 50-km radius (for ease of performing the study and reducing attrition).

#### Exclusion Criteria

The exclusion criteria were as follows:

Patients who are discharged against medical advice before the completion of treatment.Patients who are referred to other hospitals for various reasons.Patients or patients whose kin refused to give consent to participate in the study.Readmission and emergency department visits other than drug-related problems.

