#### Study Enrollment Phase

Once potential participants are deemed eligible, we will proceed with the enrollment process. The collection of baseline data on participants’ medication profiles, medical history, and other relevant information will be performed. The participants’ demographic details and contact information for follow-up will also be documented. Using tools such as MAI and START/STOPP criteria, we will evaluate the incidence of inappropriate medications after 24 hours of admission at baseline and during hospitalization every third day.

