**Intervention (CMR^f^)**									
	Medication history	✓		✓		✓			
	Medication reconciliation	✓		✓		✓			
	Medication review	✓		✓		✓			
	Collaborative team meeting	✓		✓		✓			

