#### Secondary End Points

The secondary end points were as follows:

Costs involved in the implementation of CMR in Indian health care settings (tertiary health care settings perspective).Change in the number of potentially inappropriate medications from hospital admission to discharge due to CMR.Change in the MAI score from hospital admission to discharge due to CMR.Number of medication-related hospital admissions from the day of discharge to 30 days post discharge.

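### Discharge against advice and referral out are listed as eligibility exclusions but can occur only after enrolment, and the readmission item does not say whether it removes patients or events

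*Protocol article*

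**What the plan says.** The Exclusion Criteria section of the protocol article has four items. Refusal of consent is known at enrolment. The other three are:

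- "Patients who are discharged against medical advice before the completion of treatment"
- "Patients who are referred to other hospitals for various reasons"
- "Readmission and emergency department visits other than drug-related problems"

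The Study Enrollment Phase section settles eligibility first: "Once potential participants are deemed eligible, we will proceed with the enrollment process". Table 1 ticks eligibility screening and informed consent at day 1. It ticks every CMR activity, including "Collaborative team meeting", at day 1, every third day and discharge. MAI and STOPP/START are assessed "at baseline and during hospitalization every third day", and again on the discharge prescription.

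Under Study Period and Duration, "participation will last from admission until 30 days after discharge from the hospital". The Follow-Up Phase section has field investigators ask by telephone about any hospital admission or emergency visit, and AT-HARM10 then identifies the medication-related admissions. The secondary end points include the admission-to-discharge changes in MAI and in potentially inappropriate medications, and "Number of medication-related hospital admissions from the day of discharge to 30 days post discharge".

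The Sample Size section gives 280 participants, from a 28% prevalence, an effect of 10%, 80% power and a 5% significance level. It states no allowance for losses and does not say whether excluded patients are replaced.

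**The concern.** An exclusion criterion should rest on facts known when the patient is enrolled. Discharge against advice and referral out are events of the index stay. With eligibility, consent and the first review on day 1, the two rules can act only by taking out patients who have already consented and begun CMR, apart from the few who leave before enrolment is complete. The plan rests on a single-group before/after comparison, so choosing who is analysed by how the stay ended can shift the result with no control group to reveal it.

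The readmission item raises a separate problem. Medication-related admission within 30 days is an end point, and AT-HARM10 decides which admissions qualify. If a patient is dropped because a readmission was judged not drug-related, membership of the analysed set is decided by the outcome classification.

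At stake are the efficacy results: the MAI and inappropriate-medication changes, any medication-related admission rate, and the precision expected from 280 patients.

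**Working it through.** **1. Timing of each item against day 1**

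| Exclusion item | When it becomes known | Usable at day-1 screening? |
|---|---|---|
| Refusal of consent | Day 1 | Yes |
| Discharge against advice | Later in the index stay | No |
| Referral to another hospital | Later in the index stay | No |
| Non-drug readmission or emergency visit, read as post-discharge | Up to 30 days after discharge, once the cause is judged | No |

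**2. The stated 280**

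Inputs from the Sample Size section: 28% before; 18% after (the 10% effect read as percentage points); 5% level (taken as two-sided); 80% power. With admission and discharge status assumed independent within a patient:

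- Discordant share: D = 0.28 × 0.82 + 0.72 × 0.18 = 0.2296 + 0.1296 = 0.3592
- McNemar formula: n = [1.960√D + 0.842√(D − 0.10²)]² / 0.10² = 279.6, so 280

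The stated figure is reproduced, with nothing added for losses. The article does not name its formula, so this is a reconstruction.

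**3. Power if the analysed number falls**

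The documents give no loss rate. Assume 5% to 15% leave against advice or are referred out and are not replaced: 280 × 0.95 = 266 and 280 × 0.85 = 238. Power = Φ{[0.10√n − 1.960√D] / √(D − 0.10²)}, where a within-patient correlation r lowers D by 2r√(0.28 × 0.72 × 0.18 × 0.82):

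| Correlation r | D | n = 280 | n = 266 | n = 238 |
|---|---|---|---|---|
| 0 | 0.359 | 0.80 | 0.78 | 0.73 |
| 0.2 | 0.290 | 0.88 | 0.86 | 0.82 |
| 0.3 | 0.256 | 0.92 | 0.90 | 0.87 |
| 0.5 | 0.187 | 0.98 | 0.97 | 0.95 |

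Power drops below 80% at zero correlation. At 0.2 or more it stays above 80% even with a 15% loss.

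**4. The readmission item, read as a patient exclusion**

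Let m be the per-patient risk of a medication-related admission and q the share of patients removed for a non-drug readmission or emergency visit. The rate becomes m/(1 − q). Neither value is in the documents. With an assumed 14 events in 280 (5.0%):

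| q | Patients left | Rate | Multiplier |
|---|---|---|---|
| 10% | 252 | 14/252 = 5.6% | 1.11 |
| 20% | 224 | 14/224 = 6.25% | 1.25 |

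The multiplier is the same for any m. The count of 14 does not change unless a removed patient also had a medication-related admission.

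**5. The same item, read as an event-counting rule**

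Non-drug events are not counted and nobody leaves the denominator. The rate stays 14/280 = 5.0%.

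**The case against.** The strongest objection concerns the readmission item. The other three exclusions begin with patients; this one names events. The follow-up section asks about any admission or emergency visit and then classifies the admissions, which fits a rule about which events count. On that reading nothing is inflated. The stated end point is also a number of admissions with no denominator, and it has no before value, so no stated contrast is distorted. This stands. A reader might infer that the plan inflates the medication-related admission rate; the documents support that only under the patient-exclusion reading, and the size rests on assumed rates. What survives is that an item in a patient eligibility list can be applied in two ways by the two sites.

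Second, a reader might infer that the trial will be underpowered. The documents do not support this either: the shortfall needs near-zero within-patient correlation, which is a pessimistic assumption for paired prescriptions, and no replacement of excluded patients. The plan is silent on both.

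Third, a reader might infer that the exclusions drop sicker or dissatisfied patients and so flatter CMR. Nothing in the documents fixes that direction.

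Fourth, handling of missing discharge data is commonly left to a full protocol or analysis plan. That is fair for the method of handling. It does not cover a rule the article does state and that conflicts with its own schedule.

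Finally, carrying the last in-hospital value forward is a debatable single imputation. For a patient who leaves before the first repeat assessment, it forces zero change. The fix therefore should not rest on that alone.

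**Conclusion.** The point holds in a limited form. The conflict over discharge against advice and referral out is on the face of the document and needs no assumption: both are listed as eligibility criteria, and neither can be known when eligibility is settled. Following the text makes the MAI and inappropriate-medication comparison completers-only, with a bias whose direction and size cannot be derived from the documents.

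The effect on power is possible but not established. At an assumed 5% to 15% unreplaced loss, it ranges from a fall to 0.78 to 0.73 at zero correlation to no fall below 0.80 at a correlation of 0.2 or more.

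The readmission item is ambiguous. Any per-patient rate is inflated by 1.11 to 1.25 under one reading, at an assumed 10% to 20% removed, and not at all under the other; the stated count is essentially unchanged.

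The primary end point, facilitators and barriers, is not affected. The efficacy end points are secondary, so this should be fixed but does not undermine the study.

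**What to change.** - Restrict the exclusion criteria to facts known at enrolment. Remove discharge against advice, referral out, and non-drug readmission or emergency visit from the list.
- Keep every consented, enrolled patient in the analysis set. For those without a planned discharge assessment, use the MAI and STOPP/START assessments already collected every third day, for example in a repeated-measures analysis. If the last in-hospital value is used instead, give the completers result as a sensitivity analysis.
- Report medication-related admissions over all enrolled patients. Count non-drug readmissions and emergency visits as non-events, with the patient kept in the denominator. State this in the end-point definition, which also settles the ambiguity.

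The cost is a change of wording, some extra analysis, and some missing discharge or follow-up data to handle. The in-hospital assessments and the telephone questions on all admissions are already planned. If recruitment has finished, the analysis-set rule can still be corrected provided data on the removed patients were kept.
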